# REVIVE-HF: rehabilitation with immersive virtual reality and exercise in hospitalized patients with heart failure—a randomized controlled trial protocol

**DOI:** 10.1186/s13063-026-09430-y

**Published:** 2026-01-28

**Keywords:** Virtual reality, Heart failure, Rehabilitation

## Abstract

**Background:**

Heart failure (HF) is a chronic condition characterized by significant functional limitations, with exercise intolerance as a major determinant of reduced quality of life. Supervised aerobic exercise is a core intervention in cardiac rehabilitation, yet adherence and tolerance may be hindered by physical and motivational factors. Immersive technologies such as virtual reality (VR) have shown potential to increase engagement and positive perceptions during exercise. This study aims to evaluate the influence of VR on tolerance to cycle-ergometer aerobic exercise in hospitalized patients with HF.

**Methods:**

We will conduct a randomized, controlled, parallel-group trial with 1:1 allocation. Adult inpatients with a diagnosis of HF will be screened for eligibility and randomly assigned to two groups: control (cycle-ergometer aerobic exercise) and intervention (the same exercise combined with an Meta Quest 2 VR device). Each participant will complete a single session of up to 20 min, consisting of five blocks of 3 min of continuous pedaling interspersed with one-minute passive rests, with early termination in case of intolerance. The primary outcome is effective exercise time (minutes) until interruption due to physical limitation or symptoms. Secondary outcomes include rating of perceived exertion, hemodynamic parameters, exercise enjoyment (PACES) and usability of the technology (SUS, intervention group only).

**Discussion:**

This study will investigate whether VR can improve tolerance to aerobic exercise during hospitalization for HF, potentially providing preliminary evidence to guide the use of immersive technologies in cardiac rehabilitation. If benefits are observed, VR could be incorporated as a complementary tool to optimize adherence, motivation and safety in supervised exercise programs in this clinical context.

**Trial registration:**

The trial was registered in the Brazilian Clinical Trials Registry (ReBEC), under the identifier RBR-4hrmkzz, on March 11, 2022.

**Supplementary Information:**

The online version contains supplementary material available at 10.1186/s13063-026-09430-y.

## Introduction

### Background and rationale {9a}

Among chronic noncommunicable diseases, cardiovascular diseases (CVD) are a major public health concern [1, 2], with heart failure (HF) being one of their most relevant chronic manifestations. HF is a clinical syndrome characterized by classic symptoms such as fatigue and dyspnea, which may be accompanied by signs such as jugular venous distension, pulmonary congestion and peripheral edema. These symptoms result from structural and/or functional cardiac changes leading to reduced cardiac output and/or increased intracardiac pressures at rest or during exertion [3]. Even when stable and well-compensated, HF commonly presents with exercise intolerance as a primary symptom, negatively affecting functional capacity and independence in activities of daily living, thereby impairing quality of life. Additionally, HF treatment involves complex regimens, including multiple medications, fluid control and frequent medical visits, which may increase burden on patients and families, limit social interactions, and lead to isolation [4].

Cardiac rehabilitation (CR) is an essential intervention to improve physical, psychological and social conditions in individuals with CVD, preserving and promoting quality of life and reducing risk factors. It is recognized as an effective and low-cost nonpharmacological treatment for patients with HF. Despite well-documented benefits and strong guideline recommendations, fewer than 20% of patients with HF participate in CR programs globally [5, 6], with rates as low as 1–3% reported in Brazil [7, 8]. Barriers to CR participation are multifactorial and include patient-level factors (lack of knowledge, exercise fear, low self-efficacy, comorbidities, lack of motivation), logistical barriers (distance, transportation, time conflicts, cost), health system factors (limited program availability, lack of physician referral) and environmental factors (lack of social support) [9, 10]. Notably, many patients perceive conventional CR programs as repetitive and monotonous, contributing to poor adherence and high dropout rates. This underscores the urgent need for innovative strategies to enhance patient engagement—particularly by promoting positive exercise experiences and exploring methods that increase motivation and facilitate adherence to physical activity, especially in resource-limited acute care settings.

Virtual reality (VR) has emerged as a promising technology to enhance CR engagement and adherence. Unlike conventional CR methods, which may be repetitive and less engaging, VR systems enable enjoyable activities with therapeutic purpose and interaction with virtual environments tailored to rehabilitation needs [11, 12]. VR is hypothesized to enhance engagement and adherence through several interconnected psychological and physiological mechanisms: (1) immersive environments reduce perceived exertion and distract from unpleasant physical sensations [13]; (2) VR fulfils core psychological needs (autonomy, competence, relatedness) as described by Self-Determination Theory [14]; (3) gamified elements and real-time feedback activate brain reward systems, promoting self-efficacy and behavioral persistence [15]; and (4) immersive experiences significantly reduce anxiety while improving mood states, which may enhance willingness to participate in rehabilitation [12, 16]. These mechanisms suggest that VR may be particularly valuable for acutely hospitalized HF patients, who often experience high exercise-related anxiety, low motivation and multiple barriers to traditional rehabilitation.

Preliminary evidence from our pilot study [17] demonstrated the feasibility of immersive VR exercise in hospitalized HF patients, with participants reporting enjoyment (Physical Activity Enjoyment Scale scores). However, rigorous evidence from a randomized controlled trial is needed to establish definitive clinical efficacy and justify broader implementation.

This trial aims to rigorously evaluate the efficacy of immersive VR aerobic exercise in enhancing exercise tolerance and patient satisfaction in hospitalized HF patients. Primary objective: To compare total exercise time between VR and standard cycle ergometer exercise. Secondary objectives: To assess between-group differences in perceived enjoyment (PACES) [18, 19], and system usability (SUS) [20, 21], as well as physiological responses.

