#### Secondary objectives

To compare exercise enjoyment between groups using the Physical Activity Enjoyment Scale (PACES).To assess the usability of immersive VR with the System Usability Scale (SUS).To compare safety and physiological responses (adverse events, vital signs and VR-related symptoms) between groups.

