#### Secondary outcomes

Exercise time and clinical parameters (systolic/diastolic blood pressure, respiratory rate, peripheral oxygen saturation, heart rate and rating of perceived exertion) during cycle-ergometer exercise with and without VR. These parameters will be measured across the exercise session, comparing the two approaches.Usability of the VR system during exercise, assessed using the System Usability Scale (SUS) [11, 12] administered after the session (intervention group): ease of use, comfort and perceived immersion.Patient satisfaction with the exercise experience, comparing sessions with and without VR, measured using the Physical Activity Enjoyment Scale (PACES) [13, 14].

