**POST-EXERCISE ASSESSMENTS**				
Total exercise time (minutes) (g)				X
Recovery vital signs				X
SUS—VR group only (i)				X
PACES (h)				X
Adverse events assessment (j,k)				X

a) Single-session design: Only ONE exercise session per participant during hospitalization.

b) Timepoints: Enrollment → Randomization → Intervention → Post-Exercise/Close-Out. No follow-up.

c) Both groups identical protocol except: VR group receives immersive VR headset; control group receives standard cycle ergometer.

d) Hospital Anxiety and Depression Scale (HADS): 14-item self-report questionnaire assessing anxiety (7 items, score 0–21) and depression (7 items, score 0–21) during acute hospitalization [24, 25]

e) Continuous vital signs monitoring: Blood pressure (BP, mmHg, systolic/diastolic), heart rate (HR, bpm), peripheral oxygen saturation (SpO₂, %) and respiratory rate (RR, breaths/min) recorded every minute throughout exercise and recovery period via automated monitors and continuous 12-lead ECG.

f) Session termination criteria: Immediate termination triggered if Rating of Perceived Exertion (RPE) ≥ 5 (‘hard’ intensity) OR if any safety threshold exceeded: BP > 200 mmHg or < 80 mmHg (systolic), HR > 130 or < 40 bpm,SpO₂ < 85% or ST-segment changes on ECG.

g) Total exercise time: Cumulative pedaling time (minutes) from initiation to termination.

h) Physical Activity Enjoyment Scale (PACES): 18-item questionnaire (score 18–80); higher = greater enjoyment [18, 19]

i) System Usability Scale (SUS10-item questionnaire (score 0–100); ≥ 68 indicates above-average usability; ≥ 70 considered acceptable for clinical implementation [20, 21]

j) Adverse events: Serious (requiring intervention) vs. non-serious. Documented immediately post-exercise.

k) Real-time data collection: All vital signs, RPE, observations recorded by physiotherapist on paper CRF during exercise; transferred to REDCap same day.

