## Discussion

This study addresses a relevant gap in inpatient cardiac rehabilitation by exploring the use of VR to enhance tolerance to aerobic exercise among hospitalized patients with HF. We hypothesize that VR during exercise may increase engagement, improve patient experience and favour adherence to rehabilitation programs even in hospital settings.

Practical and operational challenges typical of hospital environments are anticipated, such as resource availability, integration with routine care and logistics to schedule exercise sessions without disrupting clinical activities. Rigorous protocol adherence and precise data collection require continual communication between the research team and clinical staff. Although innovative, VR requires adequate training to ensure safe and effective use and to minimize technical issues or patient discomfort.

Critical aspects include tight safety monitoring given the fragile clinical condition of patients with HF and the protection of confidentiality in accordance with ethical and regulatory standards. These challenges will be mitigated through structured safety protocols, trained personnel, and continuous supervision during the intervention.

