## Future directions and expected outcomes

Our pilot study [17] demonstrated feasibility of immersive VR exercise in hospitalized HF patients. This REVIVE-HF trial represents a rigorous advancement with adequate sample size, randomized design and predefined outcomes. We expect the VR group to achieve longer exercise duration and higher enjoyment (PACES) and usability (SUS) scores compared to controls. If confirmed, this protocol could be adapted to other hospital contexts and incorporated as a complementary resource in cardiac rehabilitation programs, contributing to innovation in acute care.

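### A between-group SUS comparison is stated although only the VR arm completes the SUS, and VR participants stopped at familiarisation have no scheduled SUS

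*Protocol article*

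**What the plan says.** Two places in the protocol article describe the SUS as a comparison between arms. In Background and rationale {9a} the secondary objectives read "To assess between-group differences in perceived enjoyment (PACES) [18, 19], and system usability (SUS) [20, 21". Future directions and expected outcomes predicts that the VR group will have "higher enjoyment (PACES) and usability (SUS) scores compared to controls".

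The rest of the article treats the SUS as a one-arm measure:

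- Abstract, Methods: "usability of the technology (SUS, intervention group only".
- Outcomes {16}, Secondary outcomes: the SUS is "administered after the session (intervention group").
- Participant timeline {18}: the SUS row is marked for the VR group only. Footnote i explains the 0–100 score, with 68 as the above-average mark and 70 as the mark for clinical acceptability.
- Plans for assessment and collection of outcomes {25a}: a 10-item form for the VR group straight after exercise, with questionnaires typically completed 5–10 minutes after the exercise ends.
- Objectives {10}, Secondary objectives: "To assess the usability of immersive VR with the System Usability Scale (SUS"), with no comparison.

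Under VR familiarization in {15a}, a participant with significant discomfort while trying the headset does not go on to the exercise.

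**The concern.** A secondary objective that asks for a difference between arms needs scores from both arms. The control arm has no VR system to rate and is never given the form, so two sentences promise a result that the trial cannot report. If they stand, the final report must either leave a stated objective unanswered or redefine it after the data are in.

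The second issue is who contributes to the one-arm mean. Participants who put the headset on and cannot continue are those for whom the system worked least well. If the form is tied to the end of exercise, they drop out of the usability estimate because usability was poor. Harms {17} also lists the SUS among the tools for picking up VR-related problems in the intervention group, so the gap falls where the information is most relevant.

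**Working it through.** **Step 1: can the between-group SUS contrast be estimated?** No arithmetic is needed, only the sections side by side.

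| Section | SUS as comparison or one-arm | Who completes it |
|---|---|---|
| Background and rationale {9a} | comparison | not stated |
| Future directions | comparison with controls | not stated |
| Objectives {10} | one-arm | not stated |
| Abstract, Methods | one-arm | VR group |
| Outcomes {16} | one-arm | VR group |
| Participant timeline {18} | one-arm | VR group |
| Data collection {25a} | one-arm | VR group |

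Control-arm SUS observations = 0 by design. A difference in means with one empty arm is not estimable, whatever the sample size. No SUS figure is stated in the plan, so there is none to reproduce.

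**Step 2: what can be estimated?** A one-arm mean. Its 95% half-width is t(0.975, n−1) × SD / √n.

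- n = 30 (planned VR arm): 0.373 × SD.
- n = 27 (30 × 0.90, using the 10% dropout assumed in Sample size {19}): 0.396 × SD.

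The documents give no SD for the SUS. With an assumed SD of 15 to 20 and n = 30, the half-width is 0.373 × 15 = 5.6 to 0.373 × 20 = 7.5 points. The two benchmarks in footnote i differ by 2 points, so the interval will usually not separate them. That is a reason to report the interval with the mean.

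**Step 3: who is left out of that mean?** Familiarisation applies only to the VR arm, so it comes after allocation. A participant stopped there is a randomised VR participant who has worn the headset. The exercise does not take place, and the SUS is scheduled after exercise. No section schedules a SUS for this person.

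**Step 4: direction and size of the effect.** Let f be the share of headset wearers stopped at familiarisation, m₁ the mean SUS of those scored, and m₀ the mean that the unscored would have given.

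Mean over all wearers = (1 − f) × m₁ + f × m₀, so the reported mean is too high by f × (m₁ − m₀).

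This is positive whenever m₀ < m₁, which is to be expected for people stopped by discomfort. The documents give none of f, m₁ and m₀. Purely as illustration, with m₁ = 76 and m₀ = 40 (both assumed):

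- f = 0: no effect.
- f = 10%: 0.9 × 76 + 0.1 × 40 = 72.4, so the reported mean is 3.6 points too high.
- f = 20%: 0.8 × 76 + 0.2 × 40 = 68.8, so it is 7.2 points too high.

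Halving the assumed gap between m₁ and m₀ halves these figures. They show how the effect scales and are not a forecast.

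**The case against.** The strongest reply is that the formal parts of the plan are sound. Objectives {10} asks only about usability of VR and agrees with the outcomes, schedule and data-collection sections. The comparison appears in one Introduction sentence and one closing sentence, and no sample size or specified test depends on it. This stands, and it makes the point a contradiction to be edited out. It does not remove the point, because the article still carries two versions of one secondary objective and repeats the unanswerable one as an expected result.

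On coverage, it can be said that the article never states that participants stopped at familiarisation get no SUS, that those who stop during exercise still reach the post-exercise assessment, and that no test against 68 or 70 is planned. All three are correct. The gap is confined to those stopped before exercise, and it is a matter of what is scheduled, not of an explicit exclusion. Their cybersickness would still be reported as an adverse event under Harms {17}. What is lost is their usability score.

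A reader might go further and infer that better adherence is a second aim the design cannot answer, since the Discussion hypothesises that VR may "favour adherence to rehabilitation programs even in hospital settings", the abstract says "VR could be incorporated as a complementary tool to optimize adherence, motivation and safety", and the timeline specifies "Single-session design: Only ONE exercise session per participant during hospitalization". The documents do not support that reading. Adherence is not among the objectives or outcomes, the statements are conditional, and Trial design {12} and the single-session rationale already call the work foundational and preparatory to longitudinal studies. The section on adherence strategies {15c} uses the word for attending and completing the one session, which is a different and observable matter.

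A reader might also infer that safety should be dropped from the conclusions, because 0 events in 30 would still allow a rate of up to 1 − 0.025^(1/30) = 11.6%. That shows imprecision only. Safety is a listed secondary objective with a planned between-group comparison in Harms {17}.

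**Conclusion.** The contradiction is certain and rests on no assumption: two sentences state a SUS comparison with controls, and the plan collects no control SUS scores. The objective as worded in Objectives {10} can be answered.

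The coverage gap holds as the text stands. Its direction, a usability mean that is too favourable, is probable. Its size is unknown, because it depends on how many participants stop at familiarisation and how they would have scored; it is zero if none stop. It would be wrong to say that the SUS mean is shown to be biased, or that it comes only from people who tolerated the device.

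Neither part touches the primary outcome or its analysis. A minor remainder is that the Discussion's hypothesis on adherence to rehabilitation programmes is not tested by a single session without follow-up.

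**What to change.** 1. **Background and rationale {9a} and Future directions.** Align both with Objectives {10}: PACES is compared between groups, and the SUS is summarised in the VR group only, as a mean with 95% CI read against the benchmarks in footnote i of the timeline. Remove the SUS from the expected comparison with controls.
2. **Outcomes {16} and data collection {25a}.** State that the SUS is given to every VR-arm participant who wore the headset, including those stopped at familiarisation. Report how many were in that position. This changes only who receives the form, not the rule on who proceeds to exercise.
3. **Discussion (minor).** Label adherence to rehabilitation programmes as a question for later multi-session studies.

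The cost is a few edited sentences, a small number of extra 10-item forms and possibly a slightly lower SUS mean. Randomisation, sample size and treatment are unchanged. Recruitment is stated to run from 10 November 2025 to 10 November 2026, and a SUS not taken at the time cannot be recovered later, so the second change is worth making promptly.

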### Explanation for the choice of comparator {9b}

The comparator is standard aerobic cycle-ergometer exercise, which represents the current clinical standard for inpatient cardiac rehabilitation at Hospital São Paulo and aligns with guideline-recommended practice for cardiac patients. By comparing immersive VR exercise to identical standard exercise (matching in duration, intensity prescription via modified Borg Scale, physiological monitoring and supervision), this design isolates the specific effect of immersive VR technology while controlling for exercise intensity, therapeutic context and clinician supervision.

#### Rationale for active comparator design

This approach addresses a critical scientific question with direct clinical relevance: Does immersive VR technology enhance exercise tolerance and satisfaction beyond the established benefits of supervised aerobic exercise? By maintaining identical exercise parameters across groups, we isolate the VR-specific contribution while avoiding confounding from:Differential exercise intensitiesUnequal clinician attentionVarying physiological monitoring procedures

This pragmatic, active comparator design maximizes clinical applicability and generalizability to practice settings where both immersive VR and standard exercise represent feasible rehabilitation options.

### Objectives {10}

#### Primary objective

To evaluate the effect of immersive VR on exercise tolerance during cycle-ergometer aerobic exercise in hospitalized patients with HF.

#### Secondary objectives

To compare exercise enjoyment between groups using the Physical Activity Enjoyment Scale (PACES).To assess the usability of immersive VR with the System Usability Scale (SUS).To compare safety and physiological responses (adverse events, vital signs and VR-related symptoms) between groups.

## Methods: patient and public involvement, and trial design

### Patient and public involvement {11}

This study was prospectively registered prior to the publication of the SPIRIT 2025 guidance, which introduced formal requirements for patient and public involvement reporting. Consequently, structured patient and public involvement was not incorporated into the original protocol design and registration.

However, the research question and study design were informed by extensive clinical experience with hospitalized heart failure patients and awareness of documented barriers to exercise-based rehabilitation participation.

Planned involvement in dissemination and future research phases:Following publication of primary results, we are committed to engaging patients and the public in disseminating and interpreting findings through the following activities.Lay summary and patient materials: A simplified summary of study methods, results and implications will be developed in Portuguese and English for distribution to the public.Public seminars: Patient education seminars will be organized to present findings directly to heart failure patients, families and caregivers.Healthcare provider communication: Findings will be disseminated to healthcare providers through professional conferences and publications.Future research collaboration: For longitudinal studies building on REVIVE-HF findings, formal patient and public involvement structures will be established during the design phase, including patient co-investigator roles where appropriate.

The research team recognizes the value of patient and public voices in health research and commits to transparent, accessible communication of results to all stakeholders.

